##### Sample Size for Biochemical Risk Factors

An approximate sample of 1600 participants, that is, 400 in each arm, has been estimated. This sample size will help to detect an effect size of 10% mean difference from baseline with 90% power, 95% CIs, assuming 10% sample wastage. These 1600 participants would be a randomly selected subset of the 12,000 respondents (as specified for assessing the change in behavioral risk factors). The random sampling will be performed using the “sample_n” function of “dplyr” package in R software (version 4.1.2; R Foundation for Statistical Computing).

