### Randomization

The proposed study will have 4 arms: 3 intervention arms and 1 control arm. The unit of randomization would be PHCs and each of the 4 PHCs will be randomly allocated using a simple randomization technique through the lottery method to 1 of the 3 intervention arms or to the control arm. The primary strategy in this study would be health promotion by creating change agents. The 3 intervention arms would differ in the source of change agents. The 3 interventions in this proposed study would be with (1) school students as change agents, (2) VHNSC members as change agents, and (3) women’s SHG members as change agents.

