##### Baseline Data Collection (Second Month to Fourth Month)

A baseline assessment of the prevalence of NCD-related modifiable risk factors, that is, obesity, addiction, stress, and dietary practices, including salt consumption, physical activity, and hypertension or prehypertension will be conducted using the STEPS approach developed by the World Health Organization (WHO) [27]. The study questionnaires will include sociodemographic details, NCD risk factor survey, stress questionnaire, anthropometry, and blood pressure measurements. The details of these tools are given in a later section. Sample size was estimated separately for behavioral and biochemical risk factors by using G*power software (version 3.1; Institute for Experimental Psychology) for behavioral as well as biochemical risk factors.

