#### Statistical Analysis Plan

The primary outcome variable for this study would be the prevalence of various modifiable NCD risk factors as compared to baseline. Descriptive analysis will be performed using proportions with 95% CIs. For the quantitative information, difference in differences analysis using *Z*-test for differences between proportions of independent samples and ANOVA or multivariate analysis of covariance will be used to find out the effectiveness of the intervention between the intervention and the control groups. Here, the 3 interventions will be evaluated independently to demonstrate the feasibility and efficacy of each of the 3 intervention modalities. In addition, multivariate regression will be performed for finding the determinants of the risk factors, and exploratory factor analysis will be performed to explain the observed variances between intervention and control groups. For the qualitative data, thematic content analysis will be performed.

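### The 90% power stated for the 1600-person biochemical sample is for a change from baseline, not for the planned intervention-versus-control difference in differences, and the stated inputs do not determine 1600

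*Protocol article*

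**What the plan says.** Sample Size for Biochemical Risk Factors: "An approximate sample of 1600 participants, that is, 400 in each arm, has been estimated". It is meant to "detect an effect size of 10% mean difference from baseline with 90% power, 95% CIs, assuming 10% sample wastage". The section names no test, SD, baseline mean or analyte, and states no clustering allowance.

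Baseline Data Collection names the tool: "Sample size was estimated separately for behavioral and biochemical risk factors by using G*power software". Randomization gives the groups: "The proposed study will have 4 arms: 3 intervention arms and 1 control arm", with one PHC per arm.

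The Statistical Analysis Plan section names difference in differences and ANOVA or multivariate analysis of covariance, "to find out the effectiveness of the intervention between the intervention and the control groups", and says that the three interventions are assessed separately. Data Collection Tools says that a separate random sample is drawn for the endline.

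The section on behavioral risk factors includes a cluster term with value 2, printed as an intracluster correlation, for the 12,000 people from whom the 1600 are drawn.

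**The concern.** The power statement and the analysis concern different quantities. A mean difference from baseline is a change within an arm and carries the sampling error of two means. A difference in differences on independent samples carries the sampling error of four. At the same n and the same true difference it must have less power, so 90% cannot hold for both.

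A 10% difference also has no fixed meaning in sample-size terms until the SD is known as a fraction of the mean. Fasting sugar and the lipid fractions need not share one ratio, so a single 90% figure cannot be checked and need not apply to all of them.

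At stake is how a null biochemical result is read. A reader who trusts the printed sentence would take it as good evidence against a 10% intervention effect on glucose or lipids. For the planned contrast, that evidence may be much weaker.

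**Working it through.** **Inputs.** From the article: 400 per arm, four arms, 90% power, 10% wastage. Two-sided alpha of 0.05 is inferred from the 95% CIs. Analysable per arm per round: 400 × 0.9 = 360. Multiplier: 1.960 + 1.2816 = 3.2415. Assumptions, labelled as such below: SD/mean ratios and design effects.

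**1. Reproducing 1600.** Several routes were tried.

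| Route (90% power) | Before wastage | After wastage | Matches? |
|---|---|---|---|
| Four-group one-way ANOVA, f = 0.10, no clustering | 1424 total (power 0.9007) | 1424/0.9 = 1582 total | yes |
| Two arms, d = 0.10 | 2102 per arm | 2336 per arm | no |
| Paired or one-sample, dz = 0.10 | 1051 | 1168 | no |
| Two-sample, 10% of mean, SD/mean 0.41 | 354 per arm | 394 per arm | yes |
| Difference in differences, 10% of mean, SD/mean 0.29 | 354 per arm per round | about 394 per arm per round | yes |

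The ANOVA route uses the named software, the number of arms and every stated figure, and needs no undisclosed SD. The last two routes match only at particular SD/mean values that the article does not give. The last one also matches a two-sample comparison with a design effect of 2, because the variance doubles in the same way.

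**2. Detectable change within one arm.** Two independent rounds of 360:

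d = 3.2415 × √(2/360) = 0.242 SD at 90% power.

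This is 10% of the mean when SD/mean = 0.10/0.242 = 0.41.

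**3. Power of the difference in differences for that same difference.** The standard error is √(4/360) = 0.1054 SD.

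- No clustering: 0.2416/0.1054 = 2.292, and Φ(2.292 − 1.960) = Φ(0.332) = 0.63.
- Assumed design effect 2: standard error √(8/360) = 0.1491, ratio 1.621, and Φ(1.621 − 1.960) = Φ(−0.339) = 0.37.

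The unclustered drop from 90% to 63% does not depend on the SD. It follows from doubling the variance.

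**4. The same question on the ANOVA route.** If one arm differs from the other three, f = 0.10 corresponds to d = 0.10/(√3/4) = 0.231 SD. The difference in differences for 0.231 SD has power Φ(0.231/0.1054 − 1.960) = Φ(0.231) = 0.59.

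**5. Detectable difference in differences at 90% power, 360 per arm per round.** Formula: 3.2415 × √(4 × DE/360).

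| Design effect (within PHC) | Detectable difference | Equals 10% of mean if SD/mean is |
|---|---|---|
| 1 | 0.342 SD | 0.29 |
| 1.13 (assumed) | 0.363 SD | 0.28 |
| 2 (assumed) | 0.483 SD | 0.21 |

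As percent of the mean, for assumed SD/mean of 0.15, 0.30 and 0.50: 5%, 10% and 17% at design effect 1, and 7%, 14% and 24% at design effect 2.

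**The case against.** The strongest reply is that this is a condensed article. The analyte, the SD and the design effect of a subsample may well stand in the full protocol, and their absence alone would be no finding. That stands. A reader might also infer that the sample was certainly computed from f = 0.10, that it therefore was not based on a 10% difference, and that clustering was ignored. The documents support none of these as fact. No test is named, and an undisclosed SD/mean near 0.41 or 0.29 also leads to about 400 per arm. On the 0.29 route the calculation could already be for the difference in differences, or could include a design effect of 2. Silence about a clustering allowance does not show that none was used.

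It is also fair to say that ANOVA is among the planned analyses, that the sample is ample for analytes with low variability (5% detectable at an assumed SD/mean of 0.15, 7% at design effect 2), and that mean blood sugar and cholesterol are listed as secondary in Table 3.

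The reply does not rescue the printed power statement. It attaches 90% to a change from baseline, while the interventions are to be judged against control. If the 0.29 route was used, the sentence names the wrong quantity; otherwise the 90% does not carry over to the planned contrast.

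**Conclusion.** The point holds as a mismatch between a stated power and the planned comparison. If 360 analysable per arm per round give 90% power for a change within an arm, the intervention-versus-control difference in differences for the same difference has about 63% power, and about 37% at an assumed design effect of 2. The ANOVA route leads to a similar figure, about 59%, when one arm differs from the other three.

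That the figure came from a four-group ANOVA at f = 0.10 is a strong inference, not proof. A reader might go further and conclude that a 10% change could never be detected with 90% power. That is not supported: without clustering it can be, wherever SD/mean is about 0.29 or less, and the article gives no SD.

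These results assume independent samples in the two rounds, equal SD across arms and rounds, two-sided alpha of 0.05 and 10% wastage in each round. They exclude variation between PHCs. With one PHC per arm, that variation cannot be separated from the arm effect, and no within-PHC design effect covers it.

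**What to change.** Keep n = 1600. In Sample Size for Biochemical Risk Factors:

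- State the test, the effect with its SD, and any design effect actually used. Do not adopt the f = 0.10 description unless that was the calculation.
- Replace the 90% claim with the detectable intervention-versus-control difference in differences: about 0.34 SD at 90% power with 360 analysable per arm per round and no clustering, and 0.36 to 0.48 SD for assumed within-PHC design effects of 1.13 to 2.
- Convert this to percent of the mean for each analyte from the baseline SDs. Note that it equals 10% only if SD/mean is about 0.29 or less without clustering, or about 0.21 or less at design effect 2.
- Say whether the cluster term used for the parent sample of 12,000 also applies here.
- Add that, with one PHC per arm, these figures leave out between-PHC variation.

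The cost is one paragraph and a less favourable stated power.

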##### Inclusion and Exclusion Criteria

All individuals in the age group of 10-30 years, as selected through the sampling procedure described earlier who or whose parents or guardians give written informed consent, will be included in this study for evaluation of the intervention. Those experiencing severe illness or chronic diseases will be excluded from the study since their behavioral and biochemical risk factors may be influenced by their diseased status.

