**Figure 3 figure3:**
[figure not shown]
Theory of change for this study. SHG: self-help group; V-CaN: Vitalizing Community for Health Promotion Against Modifiable Risk Factors of Noncommunicable Diseases; VHNSC: Village Health Nutrition and Sanitation Committee.

**Table 1 table1:** Results framework for the proposed Vitalizing Community for Health Promotion Against Modifiable Risk Factors of Noncommunicable Diseases (V-CaN) study.

Questions	Answers	Key assumptions
What is the problem you are trying to solve?	Enabling every young person to adopt a pro-health behavior	Quality and longevity of the intervention
Who is your key audience?	All young people aged 10-30 years	Young people are receptive and value the V-CaN^a^ day messages and practice them
What is your entry point for reaching your key audience?	VHNSC^b^ members, school students, MSRLM^c^ SHG^d^ members	Health and education departments are responsive to V-CaN days and give due priority to them VHNSC members, school students, and MSRLM SHG members have interest and are committed to improving the health behavior of young people
What steps are needed to bring about the change?	Receiving administrative approvals Necessary supplies and logistics Training of trainers (supervisors) Training and capacity building of VHNSC members, school students, and MSRLM SHG members Reaching all young people aged 10-30 years through identified approaches	VHNSC members, school students, and MSRLM SHG members are able to tide over the social norms or restrictions and conduct or participate in V-CaN day activities
What is the measurable effect of your work?	Impact Obesity or overweight Prehypertension Hypertension Pro-health behavior of all young people Effect Decreased prevalence of prehypertension or hypertension Decreased prevalence of overweight or obesity Increased frequency and consumption of fruits and vegetables Increased level of physical activity Decreased stress levels Decreased tobacco use Decreased alcohol use Decreased salt intake Output V-CaN days held (number conducted or number planned) V-CaN clubs formed Proportion of young persons (10-30 years) reached	Master trainers have interest and are committed to improving the health behavior of young people Good quality in-system trainings are planned and conducted Master trainers are able to transfer the skills to VHNSC members, school students, and MSRLM SHG members

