Operational definitions of health behaviors and procedures for physical measurements and biochemical assessments will be as per the standard procedures in the WHO-STEPwise tool for the NCD risk factor surveillance. Height and weight will be measured as described in the WHO STEPwise surveillance module. For blood pressure measurements, all the readings will be recorded by trained personnel to reduce the interobserver variation. Training in all relevant techniques will be given, including care for avoiding expectation error and digit preference. The forearm will be kept at the level of the heart. The sphygmomanometer will also be kept at the level of the heart. Two readings of blood pressure will be taken: one at the beginning of the assessment and the second at midway in the assessment. If the first 2 readings differ by more than 5 mm Hg, an additional reading will be taken and the average of the 3 readings will be noted. For blood sugar and lipid profile, 5 mL of fasting venous blood sample will be collected and transferred to the central laboratory of the institute for further processing and reporting [34]. As specified in the methodology earlier, all the measurements would be performed on 12,000 participants, except for biochemical assessments, which will be performed for a random subset of 1600 participants from among the larger cohort of 12,000 participants. However, a separate random sampling will be performed as specified earlier for the endline assessment as well.

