### Ethics Approval

This study has been registered with Clinical Trials Registration India prospectively on October 28, 2020. Ethics approval has been obtained from the institutional ethics committee, Mahatma Gandhi Institute of Medical Sciences, before the start of the trial vide letter MGIMS/IEC/COMMED/79/2020. A written informed consent will be taken from all adults before enrolling in this study. For schoolchildren and adolescents, written consent will be taken from their parents and verbal assent from the participants. Treatment of study participants diagnosed with hypertension during screening will be ensured at the respective PHC. If needed, a referral to the appropriate higher center will be given to the study participants. Study participants will be interviewed and examined in private; women or adolescent girls will be examined in the presence of another female. The information in the study records will be kept strictly confidential. The identity of the study participants will be kept confidential by assigning them a unique identification number. Anonymized data would be used for scientific publications. Data quality will be checked before analysis.

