**Effectiveness**		
	Primary	Change in the prevalence of risk factors related to NCDs^d^ Feasibility of each intervention for reduction of risk factor prevalence
	Secondary	Characteristics of individuals who comply with the behavior change versus noncompliers Change in the prevalence of obese/overweight individuals, patients with hypertension or prehypertension, patients with diabetes or prediabetes Change in the mean blood pressure/blood sugar/serum cholesterol levels of population
Adoption		Proportion of V-CaN^e^ club monthly meetings held/V-CaN days celebrated out of committee Reasons for missed V-CaN club meetings/V-CaN day celebrations (comparison across the 3 arms)
Implementation		Fidelity of intervention sessions (trainings, V-CaN meetings, V-CaN days) Content delivery and satisfaction of beneficiaries Best practices, innovations, and improvisation in the 3 arms
Maintenance		Sustainability and exit plan Proportion of villages delivering the interventions during the last 6 months of the study period without active support of the study team Enabling and inhibiting factors for maintenance/discontinuation and adaptation

^a^RE-AIM: Reach, Effectiveness, Adoption, Implementation, Maintenance.

^b^SHG: self-help group.

^c^VHNSC: Village Health Nutrition and Sanitation Committee.

^d^NCD: noncommunicable disease.

^e^V-CaN: Vitalizing Community for Health Promotion Against Modifiable Risk Factors of Noncommunicable Diseases.

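### The exclusion of people with chronic diseases is not reconciled with hypertension and diabetes prevalence as outcomes, so new diagnoses can lower measured endline prevalence without any true change

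*Protocol article*

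**What the plan says.** The Inclusion and Exclusion Criteria of the protocol article define who "will be included in this study for evaluation of the intervention", and then add: "Those experiencing severe illness or chronic diseases will be excluded from the study". The reason given is that their disease may affect the risk factors being measured. No list of chronic diseases follows, and no condition is exempted.

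Several other places bear on this rule:

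- **Outcomes.** Table 3, under Effectiveness (secondary), lists "Change in the prevalence of obese/overweight individuals, patients with hypertension or prehypertension, patients with diabetes or prediabetes". Table 1 lists "Decreased prevalence of prehypertension or hypertension" among the intended effects. The Statistical Analysis Plan section says: "The primary outcome variable for this study would be the prevalence of various modifiable NCD risk factors as compared to baseline". The Introduction's list of targeted risk factors includes high blood pressure and high blood sugar.
- **Endline sample.** Data Collection Tools says that "a separate random sampling will be performed as specified earlier for the endline assessment as well".
- **Diagnosis by the study.** Ethics Approval says: "Treatment of study participants diagnosed with hypertension during screening will be ensured at the respective PHC".
- **Comparison.** The planned contrast with the control arm is a difference in differences.

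Nowhere does the article say that a person already diagnosed counts as a case at endline.

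**The concern.** An eligibility rule that removes people known to have a condition, in a survey that estimates how common that condition is, selects on the outcome. There are two consequences.

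First, prevalence is understated at both rounds by the share of cases already known.

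Second, that share need not stay constant. A person with unrecognised hypertension is eligible at baseline and counts as a case. Once diagnosed, for example by the baseline survey itself, the same person is a known case and is ineligible when the endline sample is drawn. The numerator loses cases while true prevalence is unchanged, and the error points towards benefit. A larger sample does not reduce it, and it cannot be undone later unless excluded people are recorded.

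Whether the error reaches the treatment effect depends on whether diagnosis rises by the same amount in all four arms.

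**Working it through.** **The plan's own figure.** The plan gives no figure for the share of cases that would be excluded. The only planned number used here is 3000 per arm. It reproduces and is not in dispute. For 13% against 9.75% (a 25% relative reduction), two-sided 5%, 80% power, n = [1.96·√(2p̄(1−p̄)) + 0.8416·√(p₁(1−p₁)+p₂(1−p₂))]²/(p₁−p₂)² with p̄ = 0.11375. This gives 1498 per arm. Multiplying by 2 (the article's stated clustering value, which works only as a design effect) gives 2996.

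**Formula for the artefact.** Let p be true prevalence and f the share of true cases already known and therefore excluded. Among those still eligible, measured prevalence = p(1−f)/(1−pf).

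**Inputs.** p = 5.75%, the hypertension figure that the Introduction gives for adolescents in Central India, held constant so that there is no true change. The values of f are assumptions; the article gives none.

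| Known share f | Calculation | Measured prevalence |
|---|---|---|
| 10% | 0.05175/0.99425 | 5.20% |
| 20% | 0.0460/0.9885 | 4.65% |
| 35% | 0.037375/0.979875 | 3.81% |

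**Between arms.**

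- Intervention, f from 10% to 35%: 3.81 − 5.20 = −1.39 points.
- Control, f from 10% to 20%: 4.65 − 5.20 = −0.55 points.
- False difference in differences: −1.39 − (−0.55) = −0.84 points, or 0.84/5.20 = 16% of the measured baseline.
- Equal shares in both arms (10% to 35% in each): −1.39 − (−1.39) = 0.
- With none known at baseline, endline shares of 35% against 25% give −0.56 points, and 50% against 25% give −1.42 points.

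**How much the baseline survey alone could contribute.** The share of the population aged 10-30 is not given; I assume 30% to 40%.

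- Study area of 144,000: 36,000 per arm, so 10,800 to 14,400 eligible. Screening 3000 reaches 21% to 28% of them. If every hypertension case found is later excluded, and none was known before, measured prevalence falls by 20% to 27% within each arm.
- Surveillance frame of about 120,000 in five primary health centers, taken as 96,000 in four of equal size: 24,000 per arm, so 7,200 to 9,600 eligible. Screening reaches 31% to 42%, and the fall is 30% to 40%.

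These are upper limits, because they assume that every screen-positive is diagnosed, stays in the area and age range, and is excluded. The survey runs in all four arms, so this component largely cancels in the difference in differences.

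**Diabetes.** Glucose is measured in 400 per arm. On the 144,000 basis, 400/14,400 to 400/10,800 is about 3% to 4% of those eligible. The baseline survey therefore creates far fewer known diabetes cases than hypertension cases.

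**Scale against sampling error.** With 3000 per arm per round, the standard error of the −0.84-point contrast is √[(0.0493+0.0367+0.0493+0.0444)/3000] = 0.77 points, or 0.77·√2 = 1.09 points with a design effect of 2. The illustrated bias is about 0.8 to 1.1 standard errors.

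**The case against.** The strongest reply is that the authors may not mean hypertension at all. The baseline section and the Introduction class raised blood pressure as a modifiable risk factor, the Rationale describes risk factors as leading to chronic disease, and the exclusion's own reasoning separates risk factors from diseased status. On that reading people with hypertension stay in. This stands in part: for hypertension, exclusion is a possible reading, not a certain one. It is weaker for diabetes, which the Background names in its account of chronic noncommunicable diseases. A condensed article may leave a definition to the full protocol, but what is printed here excludes without exemption a class that can contain the outcome.

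The second reply is that the one diagnostic mechanism the article describes, the baseline survey, operates equally in the control arm. This also stands: equal diagnosis gives a false effect of 0. The clubs and V-CaN days are described in terms of tobacco, alcohol, diet, activity and stress, with no blood pressure or glucose screening. Unequal diagnosis remains plausible, because only the intervention arms get added activities over 24 months of active support, but it is an inference.

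Third, outcomes that combine hypertension with prehypertension, or diabetes with prediabetes, move less than the illustration, because undiagnosed pre-states stay in the sample.

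A reader might go further and set the within-arm fall in the illustration (1.39/5.20 = 27%) beside the hypothesised 25% reduction, concluding that the artefact alone could deliver the planned effect. The documents do not support that. The 25% is stated for behavioral risk factors, the 27% is not the planned between-arm contrast, and it comes from assumed shares.

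**Conclusion.** The point holds conditionally. As printed, the exclusion conflicts with outcomes that count people with hypertension or diabetes. If known cases are treated as chronic disease, and the rule is applied again at the fresh endline sample, two things follow by arithmetic: prevalence is understated at both rounds, and within-arm prevalence falls as cases become known.

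Bias in the treatment effect needs the further condition that diagnosis rises more in an intervention arm than in control. With assumed shares of 10% to 35% against 10% to 20%, at an adolescent prevalence of 5.75%, it is about -0.84 points towards benefit; with equal shares it is 0. The part that runs through the baseline survey is smaller for diabetes than for hypertension.

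A reader might infer that the main result of the trial is compromised. That goes too far. Tobacco, alcohol, diet and activity are largely untouched. Table 3 places hypertension and diabetes prevalence among secondary effectiveness indicators, although the Introduction's list of risk factors leaves room to count blood pressure and blood sugar in the primary outcome. Severity: should fix, with medium confidence.

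**What to change.** Reconcile the Inclusion and Exclusion Criteria with Table 1, Table 3 and the primary outcome in the Statistical Analysis Plan section:

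1. Limit the exclusion to people too ill to be interviewed or measured.
2. Keep people with known hypertension, diabetes or dyslipidemia in both rounds.
3. Count anyone previously diagnosed or treated as a prevalent case, whatever the value measured on the day.
4. If known cases were already excluded at baseline, report the numbers excluded by arm, round and condition, and add them back in a sensitivity analysis where screening records allow. Relaxing the rule at endline alone would create the opposite artefact: with a 10% known share at baseline, 5.20% would become 5.75%, an apparent rise of 0.55 points.

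Keeping the same exclusion in both rounds is not a remedy, since that is how the artefact arises. The surveillance system should not be relied on to recover excluded cases, because the article describes it only as a sampling frame and does not say that it records diagnoses.

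If the authors never meant to exclude these conditions, one sentence saying so, together with the case definition in item 3, is enough. Otherwise the cost is an amendment to eligibility and outcome definitions, with a few more eligible respondents inside the same sample size and no new measurements. A question on previous diagnosis and treatment is needed if the adapted questionnaire lacks one.
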